## Abstract

**Background:**

Chronic obstructive lung disease (COPD) has diverse molecular pathomechanisms and clinical courses which, however, are not fully mirrored by current therapy. Intermittent hypoxemia is a driver of lung function decline and poor outcome, e.g., in patients with concomitant obstructive sleep apnea. Transient hypoxemia during physical exercise has been suggested to act in a similar manner. The PROSA study is designed to prospectively assess whether the clinical course of COPD patients with or without exertional desaturation differs, and to address potential pathophysiological mechanisms and biomarkers.

**Methods:**

148 COPD patients (GOLD stage 2–3, groups B or C) will undergo exercise testing with continuous pulse oximetry. They will be followed for 36 months by spirometry, echocardiography, endothelial function testing, and biomarker analyses. Exercise testing will be performed by comparing the 6-min walk test (6MWT), bicycle ergometry, and a 15-sec breath-hold test. Exertional desaturation will be defined as SpO_2_ < 90% or delta-SpO_2_ ≥ 4% during the 6MWT. The primary endpoint will be the rate of decline of FEV1(LLN) between COPD patients with and without exertional desaturation.

**Discussion:**

The PROSA Study is an investigator-initiated prospective study that was designed to prove or dismiss the hypothesis that COPD patients with exertional desaturation have a significantly more rapid rate of decline of lung function as compared to non-desaturators. A 20% difference in the primary endpoint was considered clinically significant; it can be detected with a power of 90%. If the primary endpoint will be met, exercise testing with continuous pulse oximetry can be used as a ubiquitously available, easy screening tool to prospectively assess the risk of rapid lung function decline in COPD patients at an early disease stage. This will allow to introduce personalized, risk-adapted therapy to improve COPD outcome in the long run. PROSA is exclusively funded by public funds provided by the European Research Council through an ERC Advanced Grant. Patient recruitment is ongoing; the PROSA results are expected to be available in 2028.

**Trial registration:**

The PROSA Study has been prospectively registered at clinicaltrials.gov (register no. NCT06265623, dated 09.02.2024).

## Background

Chronic obstructive pulmonary disease (COPD) is among the most prevalent chronic pulmonary diseases in the European population. Data from six European countries within the global Burden of Lung Diseases (BOLD) study suggest that COPD prevalence varies between 18 and 28% in the adult population aged 40 years and above [1]. The global number of COPD cases was estimated as 384 million in 2010, with a worldwide prevalence of 11.7% (95% CI 8.4–15.0%) and some three million deaths annually [2, 3]. The WHO recently projected the annual death rate attributable to COPD and related conditions to rise to as many as some 5 million for 2060 [4].

To counteract this predicted increase in COPD prevalence and mortality, there is an urgent need to identify COPD patients with a high risk of rapid disease progression at an early disease stage. To this end, we need to even better understand the pathophysiology of the disease; it will help us to identify novel targets for pharmacological therapy. Figure 1 schematically depicts the historical approach to COPD treatment and a possible future strategy for improved risk-adapted, personalized care of COPD patients.

**Fig. 1 Fig1:**
[figure not shown]
Currently all COPD patients are being treated by the same drugs irrespectively of their individual risk of rapid or slow progression of lung function decline, because we lack prognostic diagnostic tests (**a**). Thus, some patients have a rapid progression of their lung disease and a high risk of early mortality, but we can find out who these individuals are only when clinical events set in, depriving us of the opportunity of early, personalized and risk-adapted treatment that might bear chances to improve patients’ prognosis. Identification of ling-term risk in an early disease stage (**b**) will allow to allocate personalized, risk-adapted treatment to those with a high risk and offer the perspective of reducing the mortality rate of COPD.

Recent research has shown that the genesis of COPD starts early in life, resulting in varying lung function trajectories that may or may not ultimately lead to COPD in later life [5]. A steeper annual decline in FEV1 is associated with a higher risk of chronic respiratory disease and total mortality [6].

Traditional understanding has been that hypoxemia and pulmonary arterial hypertension may not develop but late in the disease course of COPD; however, the 2022 revision of the Global Initiative for Chronic Obstructive Lung Disease (GOLD) Guideline acknowledged that “[…] perturbations in pulmonary vasculature are major, but under recognized, drivers of symptoms and exacerbations in COPD” [7]. Indeed, vascular dysfunction and impaired endothelial nitric oxide (NO) production have been shown to occur early during the disease course [8].

The well-described poor prognosis of patients with overlap syndrome (i.e., the simultaneous presence of COPD and obstructive sleep apnoea syndrome [OSAS]) and the finding that patients with overlap syndrome show a faster decline of lung function (FEV1/FVC) over time than COPD patients without OSAS strongly underscore the hypothesis that intermittent hypoxemia is a major pathogenic factor in COPD development and progression [9, 10]. Further, both COPD and OSAS are associated with major cardiovascular co-morbidity which – importantly – is already detectable at early disease stages [8, 11] and is aggravated when both COPD and OSAS are present [10]. Hypoxemia, even when occurring intermittently, causes dysfunctional endothelium-dependent, NO-mediated vascular regulation in the pulmonary and systemic circulation in both diseases [12, 13]. Transient hypoxemia evokes adaptations in the pulmonary and systemic micro- and macrocirculation [14], and it changes pulmonary gene expression in a manner mimicking chronic lung diseases [15]. Therefore, intermittent hypoxemia may drive COPD progression via acting on the pulmonary endothelium, which has been named the “orchestra conductor in respiratory diseases” [16]. By this way, the pathophysiological mechanisms set off by hypoxia in the lungs are relevant drivers of pulmonary hypertension and right ventricular hypertrophy and failure on the one hand, but they also promote systemic cardiovascular disease and mortality.

Exertional hypoxemia as a model for provoking intermittent hypoxemia has been tested in several small studies using diverse exercise approaches. Traditionally, the 6-minute walk test (6MWT) has been used to test exercise capacity and exertional hypoxaemia in COPD patients [17]. Exertional desaturation during the 6MWT has been associated with rapid lung function decline [18] and high mortality rate [19]. However, a 15-second breath-hold-test (15-sec BHT) has also been proposed as an easily feasible alternative to test COPD patients for the presence of exercise-induced hypoxaemia [20]. Finally, bicycle ergometry remains the gold standard for exercise testing in clinical medicine; however, performing this test requires more sophisticated equipment and trained personnel than the 6MWT or the 15-sec BHT. Exertional hypoxaemia during bicycle ergometry has been shown to reflect pulmonary artery pressure in COPD patients [21].

The PROSA study (Prospective observational study to assess the influence of intermittent hypoxaemia on lung function decline, morbidity, and mortality in COPD patients) was designed to generate definite evidence for the association of exertional hypoxaemia with lung function decline and outcome in COPD patients. Beyond this, the study aims to elucidate pathophysiological mechanisms underlying this relationship and potential biomarkers that may help to better identify COPD patients at high risk of rapid disease progression at an early time point during their disease course.

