## Methods

### Study design

PROSA is a monocenter, observational, prospective cohort study. 148 patients with chronic obstructive lung disease (COPD) stages 2–3, groups B and E according to GOLD [7] will be enrolled in this clinical study. We expect that one third of our study cohort will experience exertional hypoxemia based on incidence rates reported in previous studies [22, 23]. Patients will be recalled to the study site once per year for a total of 36 months of follow-up.

The primary endpoint of the study will be the difference in FEV_1_ (LLN) over time in COPD patients with exertional desaturation versus those without exertional desaturation (exertional desaturation will be defined as oxyhemoglobin saturation by pulse oximetry (SpO_2_) < 90% or a drop of SpO_2_ ≥ 4% during a six-minute walk test [19].

Secondary endpoints have been defined as follows: (1) The difference in all-cause mortality over time in COPD patients with exertional desaturation versus those without exertional desaturation. (2) The difference in COPD-related mortality over time in COPD patients with exertional desaturation versus those without exertional desaturation. (3) The difference in frequency of hospital admissions for exacerbation of COPD in COPD patients with exertional desaturation versus those without exertional desaturation. (4) The difference in frequency of hospital admissions for causes other than exacerbation of COPD in COPD patients with exertional desaturation versus those without exertional desaturation. (5) The sensitivity and specificity of plasma biomarkers at baseline to predict the prevalence of exertional desaturation in COPD patients. (6) The sensitivity and specificity of plasma biomarkers at baseline to prospectively predict the slope of lung function decline in COPD patients. (7) The sensitivity and specificity of plasma biomarkers at baseline to prospectively predict the mortality rate in COPD patients. (8) The difference in incidence and extent of exercise hypoxemia between carriers and non-carriers of single nucleotide polymorphisms in genes of the L-arginine – dimethylarginine pathway. (9) The difference in positive and negative predictive value of bicycle ergometry, 6-minute walk test, and 15-sec breath-hold test to discriminate between COPD patients with exertional desaturation versus those without exertional desaturation.

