### Statistical analysis

Statistical analyses will be performed using the SPSS Version 27 software package (IBM Corporation, Armonk, NY, USA) and GraphPad Prism (version 6.01, GraphPad Software, San Diego, CA, USA) in the investigational center. All variables will be tested for normal distribution using the Kolmogorov–Smirnov test. Data will be expressed as mean with standard deviation (SD). Differences between groups will be tested for significance using the nonparametric Mann–Whitney U test for two groups or the Kruskal–Wallis analysis of variance for more than two groups. The Chi^2^ test will be used for comparison of categorical variables between groups. Logistic regression will be used to assess the relationship between exertional hypoxemia and mortality. The nil hypothesis for statistical evaluation of the primary endpoint will be that the difference in FEV_1_ (LLN) at 3 years of follow-up will not be different between COPD patients with exertional desaturation versus those without exertional desaturation. Exertional desaturation will be defined as oxyhemoglobin saturation by pulse oximetry (SpO_2_) < 90% or a drop of SpO_2_ ≥ 4% during a six-minute walk test [19].

Survival analyses will be performed using Kaplan–Meier curves comparing patients with or without exertional hypoxemia, and with ADMA and SDMA above or below the cut-off value determined in receiver-operated curve (ROC) analyses. Hazard ratios (HR) and 95% confidence intervals (CI) will be calculated by multivariable-adjusted logistic regression analyses. For all tests, *p* < 0.05 will be considered statistically significant. A correction of p will be performed for multiple comparisons when adequate.

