### Sample size discussion

Sample size estimation was based on analysis with repeated-measures 2-way ANOVA (baseline – 1 year – 2 years – 3 years). We assume that one third of our study cohort will experience exertional hypoxemia as reported in previous studies [22, 23], and we estimate that a 20% difference in the primary endpoint will be of clinical significance. To prove or dismiss the primary endpoint with α = 0.05 and a power of 0.90, a total sample size of 148 COPD patients stages 2–3, groups B and E according to the current GOLD guideline [7] will be included in this study after accounting for an expected drop-out rate of up to 15%.

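### Mortality hazard ratios are to come from logistic regression, which cannot give them, and with few deaths expected the claim of definite evidence does not extend to mortality.

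*Protocol article*

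**What the plan says.** The last paragraph of the Background states that the study "was designed to generate definite evidence for the association of exertional hypoxaemia with lung function decline and outcome in COPD patients". The study's full name, in the same sentence, includes morbidity and mortality.

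Under Study design, all-cause mortality and COPD-related mortality by desaturation status are secondary endpoints 1 and 2. Endpoint 7 is "The sensitivity and specificity of plasma biomarkers at baseline to prospectively predict the mortality rate in COPD patients".

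The Statistical analysis section assigns logistic regression to the relation between exertional hypoxemia and mortality. It then plans Kaplan–Meier curves and continues: "Hazard ratios (HR) and 95% confidence intervals (CI) will be calculated by multivariable-adjusted logistic regression analyses". It names no covariates. A threshold of p < 0.05 applies to all tests, with correction for multiple comparisons where adequate.

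The Sample size discussion concerns the FEV1 endpoint only: "To prove or dismiss the primary endpoint with α = 0.05 and a power of 0.90". The total of 148 is reached "after accounting for an expected drop-out rate of up to 15" percent, and one third of patients are assumed to desaturate. No death rate, target hazard ratio or power is given for mortality.

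**The concern.** Two things are wrong, and they add to each other.

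First, the model does not match the quantity. Logistic regression on death yields an odds ratio. It does not use when a patient died, and it cannot use the partial follow-up of a patient who leaves alive before month 36. Such a patient must be dropped or counted as a survivor. A result published as a hazard ratio from this model would be mislabelled, and it would not correspond to the Kaplan–Meier curves beside it.

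Second, the purpose statement promises more on mortality than a cohort of this size is likely to give. With few deaths the interval is wide, maximum-likelihood adjustment for several covariates becomes unstable, and estimates that happen to reach significance tend to be too large. Read against the Background, such an estimate could be taken as settled evidence on survival.

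**Working it through.** **Inputs from the article.** N = 148; one third desaturators (about 49 versus 99); drop-out up to 15%; α = 0.05, taken as two-sided because the article does not say.

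**Assumed inputs.** Number of deaths d and hazard ratio (HR); the article gives neither. The results are shown over a range of d.

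**Step 1: the plan's own figure.** 148 × 0.85 = 125.8, and 125 / 0.85 = 147.1, rounded up to 148. The drop-out step is therefore consistent with about 125 evaluable patients. The core FEV1 calculation cannot be rebuilt because no SD or correlation is given. There is no mortality figure to reproduce.

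**Step 2: a reference number of deaths.** 0.15 × 148 = 22.2. If every death counted as a drop-out and the allowance held, there would be about 22 deaths or fewer. Because this condition is not in the article, counts up to 44 (about 30% mortality) are also shown.

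**Step 3: precision and power.** The information for log HR is about d × (1/3) × (2/3) = 2d/9.
- Power at HR 2 = Φ(ln 2 × √(2d/9) − 1.96)
- 95% CI factor = exp(1.96 / √(2d/9))

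For d = 22, √(2 × 22/9) = 2.211. Power = Φ(0.693 × 2.211 − 1.96) = Φ(−0.43) = 33%. CI factor = exp(1.96/2.211) = 2.4.

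| Deaths (assumed) | Power at HR 2 | Unadjusted 95% CI: estimate ÷ and × |
|---|---|---|
| 10 | 18% | 3.7 |
| 15 | 24% | 2.9 |
| 22 | 33% | 2.4 |
| 30 | 43% | 2.1 |
| 44 | 58% | 1.9 |

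For HR 2, the deaths needed are (1.96 + 0.84)² / (2/9 × (ln 2)²) = 74 for 80% power, and 99 for 90% with 1.28 in place of 0.84. COPD-related deaths are a subset, so endpoint 2 is less precise again.

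**Step 4: odds ratio against hazard ratio.** Take a true HR of 2 and complete 36-month follow-up. With risk q in non-desaturators, the risk in desaturators is 1 − (1 − q)². Solve 99q + 49(2q − q²) = d.
- d = 22: q = 0.115 and 0.217; odds ratio = (0.217/0.783) / (0.115/0.885) = 2.13.
- d = 44: q = 0.237 and 0.418; odds ratio = 2.31.

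The numerical gap is small when deaths are few and grows with mortality. The loss of time at risk in censored patients comes on top and is not captured here.

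**Step 5: does penalisation help?** Simulated logistic fits were run with a true odds ratio of 2 and 148 patients; the covariates are assumed.
- At about 22 deaths, Firth penalisation lowers the SD of the log odds ratio from 0.52 to 0.49 with two covariates, and from 0.54 to 0.49 with five.
- With five covariates, the chance of an estimate above 4 falls from 26% to 19%, 16% to 12% and 11% to 8% at about 7, 15 and 22 deaths. A second run gave 23% to 17%, 17% to 11% and 13% to 9%.
- Among significant maximum-likelihood results with five covariates, the median odds ratio is 7.8, 4.7 and 3.6 at those counts. Most of this exaggeration comes from low power, which penalisation does not remove.

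The gain is modest but consistent. It was shown for logistic fits; the few-events problem being addressed is the same in a Cox model.

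**The case against.** **Deaths are not capped at 22.** A reader might infer that the 15% allowance limits deaths, and hence that a hazard ratio below about 4 cannot be detected with 90% power. The article does not support either statement. The 15% is a planning allowance, and death is never defined as drop-out. The section on spirometric assessment takes the change from baseline to the last investigation, so a patient who dies after a follow-up visit may still count for FEV1. The detectable hazard ratio at 90% power is exp(3.24/2.211) = 4.3 at 22 deaths, but exp(3.24/3.127) = 2.8 at 44. This objection stands, and 22 is used here only as a reference value.

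**Unpowered secondary endpoints are normal.** This also stands. The article claims power only for FEV1, and low power for mortality would not by itself be a fault. What remains is that the purpose statement claims definiteness for outcome without separating death.

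**Outcome is wider than mortality.** Correct. Hospital admissions are endpoints 3 and 4, and nothing here limits what they can show.

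**Consequences could be overstated.** With 22 deaths, an estimate near 1 would still exclude hazard ratios above about 2.4, and a true hazard ratio of 4 would have 87% power. So a null result would not be empty, and a large effect could be found. But the plan nowhere states that it expects an effect of that size.

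**Covariates may be left to a fuller document.** Their absence from an article is no fault. A fixed limit of one or two would also be a trade-off in an observational cohort, where confounding needs adjustment.

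**Conclusion.** The point holds for the model and for the wording about mortality. Obtaining hazard ratios from logistic regression is a mismatch on the face of the text and needs no assumption about event numbers. The numerical distortion from labelling alone is small at low mortality (an odds ratio of 2.13 for a hazard ratio of 2 at 22 deaths), but the model also discards time to death and censored follow-up.

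Definite evidence is not supported for mortality. At 22 deaths, power for a hazard ratio of 2 is about 33% and the unadjusted 95% CI spans a factor of 2.4 each way; at 44 deaths power is 58%. These figures assume the number of deaths, a one-third/two-thirds split, a two-sided 5% level and a hazard ratio of 2. The conclusion survives a doubling of the reference count. It does not extend to hospital admissions or to the FEV1 endpoint.

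**What to change.** 1. In the Statistical analysis section, estimate the mortality hazard ratios with a Cox time-to-event model, Firth-penalised and with profile-likelihood 95% confidence intervals because events are few. Patients who leave alive are censored at last contact.
2. Pre-specify the baseline covariates, and keep their number in proportion to the deaths observed.
3. In the last paragraph of the Background, do not extend definite evidence to mortality. Report the mortality endpoints as estimates with 95% confidence intervals.

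No patients, visits or procedures are added. The costs are slight shrinkage of the estimate, a more modest mortality claim, and possibly a package or extension beyond SPSS 27 and Prism for the penalised model. Penalisation will not make up for low power, so wide intervals should be expected and shown.

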## Methods

### Study design

PROSA is a monocenter, observational, prospective cohort study. 148 patients with chronic obstructive lung disease (COPD) stages 2–3, groups B and E according to GOLD [7] will be enrolled in this clinical study. We expect that one third of our study cohort will experience exertional hypoxemia based on incidence rates reported in previous studies [22, 23]. Patients will be recalled to the study site once per year for a total of 36 months of follow-up.

The primary endpoint of the study will be the difference in FEV_1_ (LLN) over time in COPD patients with exertional desaturation versus those without exertional desaturation (exertional desaturation will be defined as oxyhemoglobin saturation by pulse oximetry (SpO_2_) < 90% or a drop of SpO_2_ ≥ 4% during a six-minute walk test [19].

Secondary endpoints have been defined as follows: (1) The difference in all-cause mortality over time in COPD patients with exertional desaturation versus those without exertional desaturation. (2) The difference in COPD-related mortality over time in COPD patients with exertional desaturation versus those without exertional desaturation. (3) The difference in frequency of hospital admissions for exacerbation of COPD in COPD patients with exertional desaturation versus those without exertional desaturation. (4) The difference in frequency of hospital admissions for causes other than exacerbation of COPD in COPD patients with exertional desaturation versus those without exertional desaturation. (5) The sensitivity and specificity of plasma biomarkers at baseline to predict the prevalence of exertional desaturation in COPD patients. (6) The sensitivity and specificity of plasma biomarkers at baseline to prospectively predict the slope of lung function decline in COPD patients. (7) The sensitivity and specificity of plasma biomarkers at baseline to prospectively predict the mortality rate in COPD patients. (8) The difference in incidence and extent of exercise hypoxemia between carriers and non-carriers of single nucleotide polymorphisms in genes of the L-arginine – dimethylarginine pathway. (9) The difference in positive and negative predictive value of bicycle ergometry, 6-minute walk test, and 15-sec breath-hold test to discriminate between COPD patients with exertional desaturation versus those without exertional desaturation.

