### Study conduct and funding

The PROSA study is exclusively being funded by the European Commission as part of the European Research Council Advanced Grant Project “NO PRESSURE” (Regulation of the L-Arginine – ADMA – Nitric Oxide (**NO**) Pathway in the **P**ulmonary Vascular **Res**ponse to Hypoxia and its Role for **Sur**vival of High-Risk COPD Pati**e**nts; Proposal NO. 101,096,706).

Patients who are selected by their primary physician or pulmonology specialist as suitable for participation in the study and who are willing to undergo screening for the study will be screened by the investigators according to the inclusion and exclusion criteria. Patients who fulfil the inclusion and exclusion criteria will be informed about the scope, aims, and possible risks of the study, and after having given their written informed consent, will undergo baseline investigation (study day 1).

Investigations on study day 1 will comprise peripheral venous blood sampling and capillary blood sampling, assessment of endothelial function by measuring flow-mediated vasodilation on the forearm by ultrasound, echocardiography, spirometry, and exercise testing. The total duration of these studies is estimated to take 2.5–3 h per patient.

After completing clinical investigations on study day 1, patients will be released into ongoing primary medical care. The second investigation (study day 2) will be scheduled at 12 months after the first study day, and additional studies will take place at 24 months (study day 3) and 36 months (study day 4) after the first study day. On each of these follow-up study days, patients will be asked about their health status during the preceding 12 months, with special focus, but not exclusively, on clinical symptoms and possible exacerbations of their COPD. Thereafter, the same clinical investigations as described for study day 1 will be repeated in identical manner. After the end of study day 4, i.e. at 36 months, the study will be completed for each patient.

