Clinical follow-up with classical spirometric lung function testing will allow us to address the primary endpoint of the study, i.e., the difference in decline of FEV1 expressed as percent of the lower limit of normal as published in [26] during follow-up between patients with and without exertional hypoxemia, respectively. This is a robust endpoint that is based on a ubiquitously available clinical method, ensuring that our results will be easily transferable into routine pneumological patient care. Beyond this, we will also analyze total mortality during follow-up and hospitalization rates for COPD exacerbation and for other causes as secondary clinical endpoints.

Aside from this, we will strive to better understand the pathophysiology linking exertional hypoxemia with progression of lung disease. We have evidence supporting a role for the pulmonary L-arginine – ADMA – NO pathway in modulating the response of the lung to intermittent hypoxia, and we will test in PROSA whether L-arginine-related metabolites may be suitable as biomarkers for differentiating COPD patients with and without exertional hypoxemia and/or COPD patients with good or poor prognosis, respectively. Biomarkers have become important clinical diagnostic tools that also help in therapeutic decision making. Thus, if the biomarkers we will analyze show predictive value for differentiating COPD patient subgroups, this may aid in risk assessment in clinical routine as well. Also, therapeutic intervention in this pathway has been tested by various means in other diseases; it may help to find more personalized treatments options for the subgroup of COPD patients with exertional hypoxemia and thus stimulate future therapeutic trials. The overall hypothesis for PROSA is depicted schematically in Fig. 3.

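### The only exacerbation endpoint counts hospital admissions; the exacerbations already asked about at each follow-up visit feed no listed endpoint, although counting them would give a more powerful comparison.

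*Protocol article*

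**What the plan says.** Methods, Study design lists nine secondary endpoints. The third is "The difference in frequency of hospital admissions for exacerbation of COPD" in desaturators versus non-desaturators; the fourth is the same comparison for admissions from other causes. The Discussion repeats the restriction: besides total mortality it names "hospitalization rates for COPD exacerbation and for other causes as secondary clinical endpoints".

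Study conduct and funding describes the three follow-up visits, each with an interview covering the past year. The interview is to be held "with special focus, but not exclusively, on clinical symptoms and possible exacerbations of their COPD". No listed endpoint takes up exacerbations managed without admission.

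The Background cites guideline text that pulmonary vascular perturbations are "drivers of symptoms and exacerbations in COPD", which is not limited to admitted events.

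Statistical analysis names the Mann-Whitney U test as the general test for differences between two groups. It gives no separate method for event counts. The sample size section concerns the primary endpoint only.

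**The concern.** Admissions for exacerbation are a subset of all exacerbations. With the same patients and follow-up, restricting the count to that subset leaves fewer events and a less precise comparison. The cohort is described as being at a relatively early stage of disease, and only about one third are expected to desaturate, so the number of admissions in the smaller group could be low.

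At stake is how endpoint 3 would be read. If it shows no difference, readers may conclude that exertional desaturation is unrelated to exacerbations, when the comparison could have missed a doubling of the rate. The planned interviews could supply a broader count without another visit, but only if the event is defined in advance; the article refers to possible exacerbations without a definition.

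A second weakness concerns the test. A Mann-Whitney comparison of raw counts gives a patient who dies or drops out after one year the same standing as one observed for three. If desaturators are lost or die sooner, their counts are cut short and the difference is blurred.

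**Working it through.** **Plan's own figure.** The article states no power, detectable difference or event rate for endpoint 3, so there is nothing to reproduce for it. The 148 belongs to the primary endpoint. It cannot be rebuilt from the article, which gives no standard deviation, reference mean or within-patient correlation, and it is used here only for the number of patients.

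**Inputs from the article (Sample size discussion; Study design)**
- "a total sample size of 148 COPD patients stages 2–3, groups B and E".
- "We assume that one third of our study cohort will experience exertional hypoxemia".
- Drop-out of up to 15%; alpha 0.05, taken here as two-sided.
- Follow-up of 36 months.

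Evaluable patients: 148 × 0.85 = 125.8, about 126. One third is 42 desaturators, leaving 84 non-desaturators.

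**Assumptions (not in the article)**
- Admissions for exacerbation in non-desaturators: 0.10 to 0.20 per patient-year.
- All exacerbations in non-desaturators: 0.8 per patient-year.
- Negative binomial dispersion k from 0.5 to 2, held equal for both counts so that the contrast does not come from a different k.
- Each evaluable patient contributes 3 years.

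**Formula.** With μ0 = 3 × rate and μ1 = μ0 × RR,

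var(log RR) = (1/μ1 + k)/42 + (1/μ0 + k)/84.

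Power = Φ(log RR / SE − 1.96). The detectable ratio at 80% power solves log RR = (1.96 + 0.84) × SE.

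**Worked case, k = 1, true RR = 2**
- Admissions at 0.10: μ0 = 0.3, μ1 = 0.6. Variance = (1.667 + 1)/42 + (3.333 + 1)/84 = 0.0635 + 0.0516 = 0.1151; SE = 0.339. log 2 / SE = 0.693/0.339 = 2.04; power = Φ(0.08) = 53%.
- All exacerbations at 0.8: μ0 = 2.4, μ1 = 4.8. Variance = (0.208 + 1)/42 + (0.417 + 1)/84 = 0.0288 + 0.0169 = 0.0456; SE = 0.214. log 2 / SE = 3.24; power = Φ(1.28) = 90%.

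**Results.** Admission ranges run from a rate of 0.10 to 0.20.

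| k | Detectable RR, admissions | Detectable RR, all | Power at RR 2, admissions | Power at RR 2, all |
|---|---|---|---|---|
| 0.5 | 2.33-1.96 | 1.61 | 60-82% | 99% |
| 1 | 2.50-2.14 | 1.83 | 53-71% | 90% |
| 1.5 | 2.67-2.32 | 2.03 | 48-62% | 79% |
| 2 | 2.84-2.50 | 2.22 | 43-55% | 68% |

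For a true ratio of 1.5 over the same k range, power is 17-36% for admissions and 29-66% for all exacerbations.

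**Effect of recall loss.** If 12-month recall captured only half the events in both groups (0.4 instead of 0.8 per patient-year), the detectable ratio for the wider count becomes 1.74, 1.94, 2.13 and 2.32 at k = 0.5, 1, 1.5 and 2. It stays below the admission figures in each row, but at an admission rate of 0.20 the gap is only about 0.2.

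**The case against.** Endpoint 3 is clearly worded and consistently repeated, and it forms a coherent pair with endpoint 4. Admissions are discrete, verifiable events that need no grading from memory. The 90% power is claimed for the primary endpoint alone, so no statement in the article is shown to be false. All of this stands. It is why endpoint 3 should be kept, and why this is a weak choice on a secondary outcome and not an error.

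The wider count also has limits. With dispersion held equal, variation between patients caps the gain, and a ratio of 1.5 remains hard to detect. Outpatient events recalled over a year are under-reported. This also stands: the gain is moderate, not decisive.

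A reader might infer more than the article supports:
- That the comparison can detect only one particular ratio. Any such figure depends on an assumed rate and dispersion, so only a range is defensible.
- That a wide gap can be shown by giving admissions a higher dispersion than all exacerbations. Nothing in the article justifies unequal values.
- That the interview data are discarded. The article shows only that no listed endpoint uses them; the full protocol and analysis plan are not at hand.
- That admissions are the rarest events in the study. No rates are given, and deaths (endpoints 1 and 2) may be rarer.
- That exacerbations are asked about at every visit. The questioning is described for the three follow-up visits, not for study day 1.
- That the guideline text makes exacerbations a study hypothesis. It is background; the stated hypothesis is lung function decline.

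**Conclusion.** The concern holds as a limitation of the secondary endpoint set. The direction does not depend on the exact values: at each equal dispersion tested, the wider count detected a smaller ratio than admissions did. The size does depend on them. Under the assumptions listed, the detectable ratio falls from about 2.0-2.8 to about 1.6-2.2, and power for a doubling rises from about 43-82% to 68-99%, before any allowance for incomplete recall. Neither count is adequate for a ratio of 1.5, so a null result would need cautious reading even after the change. The point about the test is separate and needs no assumed rate: the Mann-Whitney test, if applied to raw counts as the general rule implies, takes no account of follow-up shortened by death or drop-out.

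**What to change.** Leave endpoint 3 as it is. Add one secondary endpoint: the rate per patient-year of all COPD exacerbations, defined as events treated with a systemic steroid or an antibiotic, or leading to admission, recorded at the yearly interview already planned. Analyse this and endpoint 3 with a negative binomial model and log follow-up time as offset, replacing the Mann-Whitney test on counts, and report rate ratios with 95% confidence intervals so that a null result can be judged by its width.

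Cost: one more secondary endpoint to account for under multiplicity, and a form item on treatment for each reported event; no extra visit. Recruitment is ongoing, so the change should be documented as an amendment, preferably before many follow-up interviews have accumulated. Under-reporting from 12-month recall will remain and will lower the gain; the unchanged admission endpoint is the safeguard.
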